## Abstract

**Background:**

The standard treatment for patients with unresectable locally advanced esophageal squamous cell carcinoma (ESCC) is definitive chemoradiotherapy (CRT) using 5-FU plus cisplatin. However, complete response (CR) rates are low at 11–25%, resulting in 9–10 months of median overall survival (OS). An improved therapeutic efficacy by combining immunotherapy with radiation has been reported in patients with locally advanced non-small cell lung cancer. The results using ESCC cell lines suggest sequential treatment with anti-PD-L1 agents soon after completion of CRT is the most effective combination.

**Methods:**

TENERGY trial is a multicenter, phase II, proof-of-concept study to assess the efficacy and safety of atezolizumab following definitive CRT in patients with locally advanced ESCC. The main inclusion criteria are unresectable locally advanced ESCC without distant metastasis, completion of 60 Gy of radiation plus two concomitant cycles of chemotherapy (cisplatin 70 mg/m^2^ on day 1 and 5-FU 700 mg/m^2^ on days 1–4, every 28 days), and adequate organ function. Within 6 weeks after CRT, participants will start taking 1200 mg of atezolizumab every three weeks and continue until 12 months or disease progression. The primary endpoint is the confirmed CR rate by the investigator’s assessment. Secondary endpoints include overall response rate, progression-free survival (PFS), OS, adverse events, and confirmed CR rate by central assessment. We will enroll 50 patients (40 with primary locally advanced ESCC and 10 with postoperative locoregionally recurrent ESCC). We will obtain biopsies from the primary site and will collect blood at 3 time points (before CRT, after CRT, and four weeks after the start of atezolizumab) for an exploratory biomarker study. We will analyze the phenotype of immune-competent cells, neoantigens, tumor mutational burden, PD-L1 status, and Human Leukocyte Antigen haplotyping.

**Discussion:**

The synergistic efficacies of the sequential combination of CRT and atezolizumab should improve the CR rate, resulting in survival improvement for patients with unresectable locally advanced ESCC. Because CRT is a standard treatment option for patients with early stage to locally advanced ESCC, the sequential combination of CRT and atezolizumab has the potential to change the standard ESCC treatments.

**Trial registration:**

UMIN000034373, 10/04/2018 and EPOC1802.

## Background

Carcinoma of the esophagus is an extremely devastating disease, especially when the disease invades adjacent structures such as aorta, vertebral bodies, or trachea (T4b), and becomes unresectable. According to the Comprehensive Registry of Esophageal Cancer in Japan, the incidence of T4b esophageal cancer accounts for approximately 6.7% of all patients with esophageal cancer (approximately 1500 patients per year) [1]. The standard treatment for this population is definitive chemoradiotherapy (CRT) using 5-FU plus cisplatin. However, complete response (CR) rates are low at 11 to 25%, resulting in 9 to 10 months of median overall survival (OS) [2–4]. Although new strategies have been investigated [4], the treatment regimens have not changed since 1990s.

Immunotherapy with immune checkpoint inhibitors (ICIs) has revolutionized the treatment of advanced cancers, including that of esophageal cancer. Pembrolizumab, an anti-programmed death 1 (PD-1) antibody, significantly improved OS in patients with programmed death ligand 1 (PD-L1) combined positive score (CPS) ≥10 metastatic esophageal cancer [5]. Subgroup analyses indicated higher efficacies of pembrolizumab for patients with esophageal squamous cell carcinoma (ESCC) than those for patients with adenocarcinoma, and the Food and Drug Administration (FDA) approved pembrolizumab for patients with metastatic ESCC whose tumors express PD-L1 CPS ≥10 after ≥1 prior line of systemic therapy. Subsequently, nivolumab, another anti-PD-1 antibody, showed significant OS improvement in patients with metastatic ESCC after ≥1 prior line of systemic therapy (regardless of PD-L1 status) [6].

ICIs combined with ionizing radiation are promising approaches due to their efficacies. Mechanisms facilitating the action of ICIs by radiation include increased tumor antigen release, activation of innate immune pathway, increased T-cell infiltration, augmented antigen presentation, and modulation of immunosuppressive cells [7, 8]. Indeed, in in vivo models, sequential combination of an anti-PD-1 antibody and radiation increased the proportion of tumor antigen complexes and major histocompatibility complex (MHC) molecules, enhanced lymph node cross-presentation, and increased T-cell tumor infiltration [9]. The polyclonal T-cell response also mediated out-of-field (abscopal) effects following local radiotherapy [10]. An abscopal effect from the combination of radiation and immunotherapy has also been reported in cases with different cancer types [11]. Phase I trials showed a 10–13.5% response rate for liver or lung metastases outside the radiation field [12, 13]; thus, similar efficacies may be expected for micro metastatic lesions in patients with locally advanced cancer.

According to other studies, chemotherapy and radiotherapy may mediate the release of interferon gamma (IFN-γ) produced by CD8+ T cells resulting in PD-L1 upregulations in various tumor cells [8, 14]. Our preliminary studies using both ESCC cell lines and a radiation irradiation device used in the clinical practice also reported that 60 Gy of radiation upregulated only the expression of PD-L1 and MHC Class I without affecting the expression of PD-L2 (data not shown). As lymphocytes are radiation sensitive, we hypothesized that the sequential treatment with anti-PD-L1 agents soon after completion of CRT would enhance the treatment efficacies.

Among patients with unresectable locally advanced non-small cell lung cancer, 12 months of the anti-PD-L1 antibody durvalumab following platinum-based CRT significantly improved both PFS and OS irrespective of PD-L1 expression before CRT [15, 16]. Durvalumab also had a favorable effect on the frequency of new metastases, including on the incidence of new brain metastases. The safety profile of durvalumab was consistent with those of other immunotherapy-related trials, and included a relatively high but acceptable radiation or ICI-induced pneumonitis rate.

Based on this information, we have planned a phase II proof-of-concept (POC) clinical trial to evaluate the safety and efficacy of the anti-PD-L1 antibody atezolizumab following definitive CRT in patients with unresectable locally advanced ESCC.

## Methods/design

### Study design and treatment

The TENERGY trial is a multicenter, phase II POC study to assess the safety and efficacy of a sequential combination therapy with atezolizumab following 5-FU plus cisplatin-based chemoradiotherapy (60 Gy/30 fractions without prophylactic irradiation) in patients with unresectable locally advanced ESCC without distant metastasis. This study consists of two parts: we will enroll patients with primary locally advanced ESCC into the primary locally advanced ESCC part, and patients with locoregionally recurrent ESCC after surgical resection into the postoperative locoregionally recurrent ESCC part (Fig. 1).

**Fig. 1 Fig1:**
[figure not shown]
Study design. The TENERGY trial consists of two parts. After completion of definitive chemoradiotherapy, patients with primary locally advanced esophageal squamous cell carcinoma (ESCC) will be enrolled into the primary locally advanced ESCC part (*N* = 40) Patients with locoregionally recurrent ESCC after surgical resection will be enrolled into the postoperative locoregionally recurrent ESCC part (*N* = 10)

Table 1 shows the inclusion and exclusion criteria for both parts. We will provide the intervention treatment to patients who meet all the inclusion criteria and do not meet any of the exclusion criteria. Although the CRT is not included in the protocol therapy, both chemotherapy and radiation will be stringently qualified based on the quality assurance and quality control program. We will initiate the study intervention treatment within 6 weeks after CRT completion. Patients will receive 1200 mg of atezolizumab every three weeks until 12 months (maximum of 17 doses), disease progression, patient withdrawal, investigator’s decision, pregnancy, or unacceptable toxicities (whichever comes first).

**Table 1 Tab1:** Patient inclusion and exclusion criteria

Inclusion Criteria	
Inclusion Criteria (for the primary locally advanced ESCC part)	
1. Patients with histologically confirmed primary esophageal squamous cell carcinoma, adenosquamous carcinoma, or basaloid-squamous carcinoma.	
2. Patients with primary lesion located in the thoracic esophagus based on the UICC TNM 7th edition classification, patients with invasion to cervical esophagus and/or abdominal esophagus are eligible when definitive CRT is eligible, patients with secondary lesions that are curable by endoscopic resection are eligible.	
3. Patients diagnosed as having an unresectable tumor by a pre-CRT CT scan as described below. Patients with esophageal perforation, esophagotracheal fistula, esophagomediastinal fistula, bleeding from arterial invasion, or respiratory stenosis are ineligible.	
i. The depth of the primary tumor is diagnosed as T4b (tumor invades other adjacent structures such as aorta, vertebral body, or trachea) according to the UICC TNM 7th edition and Japanese Classification of Esophageal Cancer The 11th Edition.	
ii. Regional lymph nodes and/or supraclavicular lymph node have invaded adjacent structures other than esophagus.	
4. Patients without distant metastases other than supraclavicular lymph node by pre-CRT CT scan.	
5. Patients without prior esophageal cancer treatment except for endoscopic resection before CRT.	
6. Patients for whom the CRT described below has been performed and for whom the protocol treatment can be started within 42 days after CRT completion.	
i. Chemotherapy started at CDDP 70 mg/m^2^ on day 1, 5-FU 700 mg/m^2^ on days 1–4 and 2 times every 4 weeks. Second cycle dose reductions were allowed according to the toxicities.	
ii. 60 Gy/30 fractions of radiotherapy performed without exceeding dose limitations to at-risk organs.	
7. Patients without esophageal perforation, esophagotracheal fistula, esophagomediastinal fistula, bleeding from arterial invasion, or respiratory stenosis when CRT is completed.	
Inclusion Criteria (for the postoperative locoregionally recurrent ESCC part)	
1. Patients with histologically confirmed esophageal squamous cell carcinoma, adenosquamous carcinoma, or basaloid-squamous carcinoma on surgical specimens.	
2. Patients with local (mediastinum, anastomosis) or regional (regional lymph node) recurrences after curative surgery, whose recurrences are considered treated with definitive CRT.	
3. Patients without distant metastases except those in supraclavicular lymph nodes by pre-CRT CT scan.	
4. Patients treated with neoadjuvant chemotherapy 24 months or more before start-up of any definitive CRT.	
5. Patients for whom the CRT described below has been performed and those for whom the protocol treatment can be started within 42 days after CRT completion.	
i. Chemotherapy started at CDDP 70 mg/m^2^ on day 1, 5-FU 700 mg/m^2^ on days 1–4 and 2 times every 4 weeks. Second cycle dose reductions were allowed according to the toxicities.	
ii. 60 Gy/30 fractions of radiotherapy performed without exceeding dose limitations to at-risk organs.	
6. Patients without esophageal perforation, esophagotracheal fistula, esophagomediastinal fistula, bleeding from arterial invasion, or respiratory stenosis when CRT is completed.	
Inclusion Criteria (common to both study parts)	
1. Patients 20 years or older.	
2. Patients with Eastern Cooperative Oncology Group Performance Status (ECOG PS) 0 or 1.	
3. Patients with the following organ functions within 14 days of registration:	
i. Neutrophil count ≥1200/mm^3^	
ii. Platelet count ≥75,000/mm^3^	
iii. Hemoglobin ≥8.0 g/dL	
iv. Serum albumin ≥2.5 g/dL	
v. T-Bil ≤1.5 x ULN, in the case of Gilbert’s syndrome T-Bil ≤2.5 x ULN	
vi. ALT and AST < 100 IU/L	
vii. Serum creatinine ≤1.5 mg/dL or calculated or measured values of creatinine clearance ≥45 mL/min	
viii. SpO2 ≥ 95% (room air)	
4. Women of childbearing potential with a negative urine pregnancy test within 14 days of registration.	
5. Patients who agree to take appropriate precautions to avoid pregnancy from the time of the informed consent to 5 months after the final administration of the investigational drugs.	
6. Patients with life expectancy longer than 3 months.	
7. Patients who sign written informed consent.	
Exclusion Criteria	
1. Patients with active multiple primary cancers (synchronous multiple primary cancers and multiple cancers with a progression-free period of ≤3 years from the time of enrollment), carcinoma in situ or intramucosal carcinoma curable by local resection are not included in the definition of active multiple primary cancers.	
2. Patients with active infection for which systemic treatments are needed.	
3. Patients with past or concurrent inflammatory bowel disease.	
4. Patients with past or concurrent pneumonitis or interstitial lung disease (ILD).	
5. Patients with concurrent autoimmune disease or with past chronic or recurrent autoimmune disease.	
6. Patients requiring treatment with systemic corticosteroids or immunosuppressants.	
7. Patients with past or concurrent thyroid dysfunction (hyperthyroidism or hypothyroidism).	
8. Patients with a history or finding of a cardiovascular risk:	
i. Patients with a left ventricular ejection fraction below 50%	
ii. Patients with clinically significant, poorly controlled arrhythmia	
iii. Patients with acute coronary syndrome, coronary angioplasty, or stent placement within 6 months before enrollment	
iv. Patients with class II or more severe congestive heart failure	
v. Patients with treatment-resistant hypertension	
vi. Patients wearing an implantable cardioverter defibrillator or permanent pacemaker	
9. Patients with poorly controlled diabetes mellitus.	
10. Patients positive for HIV antibody, HBs antigen or HCV antibody.	
11. Pregnant or lactating patients.	
12. Patients with a significant unstable mental disease or other medical disease that may interfere with their safety, obtaining informed consent, or compliance with the procedures for the clinical study.	
13. Patients with a history of treatment with atezolizumab, anti-PD-1 antibody, anti-PD-L1 antibody, anti-PD-L2 antibody, anti-CD137 antibody, or anti-CTLA-4 antibody or a history of any other antibody therapies or drug therapies intended to regulate T cells.	
14. Patients who are not willing to or who cannot comply with the procedures specified in the protocol.	
15. Patients unsuitable for the study due to complicated disorders affecting the assessment of toxicity according to the investigator’s judgment.	

We are conducting this study in accordance with the guidelines for Good Clinical Practice of the International Council on Harmonization of Technical Requirements for Registration of Pharmaceuticals for Human Use, as well as with the ethical guidelines for medical and health research involving human subjects. All patients are required to sign written informed consents. We registered the study in the University Hospital Medical Information Network (Clinical trial information number: UMIN000034373).

### Endpoints and assessments

The primary endpoint is the confirmed CR rate by an investigator’s assessment in the primary locally advanced ESCC part. The secondary endpoints are the confirmed CR rate by central assessment, the objective response rate (ORR) by the investigator’s assessment, the PFS, the OS, and the incidence of adverse events (AEs).

CR will be determined by both computed tomography (CT) scanning and endoscopy based on the Response Evaluation Criteria in Solid Tumors (RECIST) version 1.1 with modifications and on the Japanese Classification of Esophageal Cancer (11th edition), respectively. The schedule for both CT scans and endoscopy examinations are every 4 weeks until CR, following the confirmation of CR after more than 4 weeks, and thereafter every 12 weeks. The modified RECIST defines both measurable and non-measurable lymph nodes as those ≥10 mm and 5–10 mm in their short axis, respectively, when assessed by CT scan. According to the Japanese Classification of Esophageal Cancer, we defined the primary lesion is as CR when conditions satisfy all of the following 4 factors: disappearance of endoscopic findings suggesting the presence of a tumor, negative endoscopic biopsy findings from the area of the primary tumor, evaluable entire esophagus using endoscopy, and no endoscopic findings of active esophagitis. We defined ORR as the proportion of patients who achieve CR or partial response (PR). We defined PFS as the period from registration to progression or death from any cause and will censor it on the last day the patient is alive without progression. OS is the period from registration to death from any cause, and we will censor it on the last day the patient is alive. We will assess AEs according to the Common Terminology Criteria for Adverse Events (CTCAE) version 4.0 before administration of the investigational drug on the administration day. In the postoperative locoregionally recurrent ESCC part, we will assess the same endpoints in an exploratory manner.

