### Target sample size and statistical analyses

The reported CR rates have ranged from 11 to 25%. In this study, we estimate a rate of 20% as the CR threshold. Therefore, we calculated the sample size of the primary locally advanced ESCC part at 38 with a CR of 40% deemed promising and one of 20% deemed unacceptable (one-sided α, 0.05; β, 0.2). Under this calculation, we are planning to include a maximum of 40 patients in the primary locally advanced ESCC part. We set the planned sample size of the postoperative locoregionally recurrent ESCC part at a maximum of 10 patients in an exploratory manner. We will calculate the confirmed CR by the investigator’s assessment and its 90% confidence interval using the exact binomial method. The results will be considered statistically significant with more than 13 confirmed CR cases in accordance with both the RECIST and the Japanese Classification of Esophageal Cancer in the primary locally advanced ESCC part (i.e., CR rate ≥ 34.2%). We will also determine the confirmed CR rate by central assessment, the ORR by the investigators’ assessment, the PFS, and the OS using appropriate statistical methods. Finally, we will also tabulate the incidence of AEs in the safety population.

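### The PFS censoring date is not tied to the last CT or endoscopy, so time in contact but without examination can count as progression-free

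*Protocol article*

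**What the plan says.** All wording is from the protocol article.

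- **PFS definition** (Endpoints and assessments): "We defined PFS as the period from registration to progression or death from any cause". For patients without an event, the investigators "will censor it on the last day the patient is alive without progression".
- **OS censoring** (next sentence): "we will censor it on the last day the patient is alive".
- **Examinations** (same section): CT and endoscopy are done "every 4 weeks until CR, following the confirmation of CR after more than 4 weeks, and thereafter every 12 weeks".
- **Contact** (Study design and treatment, below Fig. 1): "Patients will receive 1200 mg of atezolizumab every three weeks until 12 months". Adverse events are assessed on each dosing day.
- **Role of PFS**: it is one of the secondary endpoints. The statistical section says only that the trial will determine "the PFS, and the OS using appropriate statistical methods". It gives no PFS target or test.

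**The concern.** Progression that is not death is found by looking for it, here with CT and endoscopy. A patient's progression-free status is therefore known only up to the last examination. The stated rule lets the censoring date run past that point for as long as the patient is known to be alive and no progression has been recorded.

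Two kinds of patient are affected. The first keeps to schedule but is seen every 3 weeks for dosing and examined less often, so the gap is bounded by the examination interval. The second stops examinations, for example after leaving treatment for a reason other than progression, but is still followed for survival. For this patient the gap has no upper limit.

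A single-arm PFS can only be read against outside figures. There is no control arm in which the same error would cancel.

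**Working it through.** **1. The plan's own figure.** The article gives no PFS figure to reproduce. Its only design calculation concerns the CR rate, "with a CR of 40% deemed promising and one of 20% deemed unacceptable", with one-sided α 0.05 and β 0.2. Taking success as 13 or more of 38 (13/38 = 34.2%, the rate that the article states), the exact binomial gives:

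- P(X ≥ 13 | n = 38, p = 0.20) = 0.0288
- P(X ≥ 13 | n = 38, p = 0.40) = 0.814

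So 38 reproduces. No PFS quantity enters, and nothing below changes it.

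**2. Unexamined time per patient.** For a censored patient the excess is the last contact date minus the last examination date.

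- On schedule without CR: at most about 4 weeks.
- On schedule after confirmed CR: at most about 12 weeks.
- Examinations stopped but patient known alive: unbounded. For illustration, a patient last examined at week 12 and known alive at week 60 is credited with 60 − 12 = 48 unexamined weeks.

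**3. Effect on the Kaplan-Meier estimate.** Each scenario simulated 60,000 patients. They were examined every 4 weeks, changing to every 12 weeks after confirmed CR, with contact every 3 weeks. From the article: the two examination intervals, the 3-week contact (applied throughout follow-up for simplicity), and CR shares of 20% and 40%. Assumed, because the article gives no figures:

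- median PFS of 20 or 26 weeks without CR, paired with 52 or 104 weeks with CR;
- 15% of events being deaths without prior progression;
- follow-up of 26 to 104 weeks;
- 0 to 30% of patients stopping examinations while still in contact, at a random time unrelated to their disease.

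52-week PFS (%), censored at last contact / at last examination (difference in points):

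| Medians without CR / with CR, CR share | 0% stop | 10% stop | 20% stop | 30% stop |
|---|---|---|---|---|
| 20/52 weeks, 20% | 24.1 / 23.4 (0.7) | 25.3 / 23.2 (2.1) | 27.1 / 23.7 (3.4) | 28.0 / 23.0 (5.0) |
| 20/52 weeks, 40% | 32.0 / 31.0 (1.0) | 32.8 / 30.4 (2.4) | 33.8 / 30.0 (3.8) | 35.4 / 30.2 (5.2) |
| 26/104 weeks, 20% | 35.6 / 34.9 (0.7) | 36.2 / 34.1 (2.1) | 37.9 / 34.6 (3.3) | 38.7 / 33.9 (4.8) |
| 26/104 weeks, 40% | 45.0 / 44.0 (1.0) | 45.6 / 43.4 (2.2) | 46.9 / 43.5 (3.4) | 47.7 / 43.0 (4.7) |

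Moving to the last examination shortens the median by 0 to 0.7 weeks with full assessment, and by 0.3 to 4.5 weeks with 10 to 30% stopping. At 52 weeks the contact-date rule gives the higher figure in every scenario.

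**4. What the change does not remove.** With full assessment, the true 52-week values in the four rows were 22.8, 30.2, 34.6 and 43.5%. The last-examination rule still exceeds them by 0.6, 0.8, 0.3 and 0.5 points. That remainder reflects progression being dated at the visit that finds it, which happens under either censoring rule.

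**5. Limits of the simulation.** It does not let an undetected progression become a recorded death. Such a death would be an event on the same date under both rules and would close part of the gap, so the figures with stopping lean high for the rates assumed. It also treats stopping as unrelated to disease. If deteriorating patients are the ones who stop, both rules overstate PFS.

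**The case against.** The strongest reply is that the wording is ambiguous rather than wrong. The PFS rule carries a condition that the OS rule lacks, namely being without progression. It could mean the last day on which that status was established, with the derivation left to the full protocol or analysis plan. That reading is possible, but the text does not state it. The article does fix a censoring date, and one that admits two different days is badly fixed for a time-to-event endpoint.

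The second reply is size. With all examinations done, the difference is about 1 point. The standard error of a 30% PFS estimate in 40 patients, before any censoring, is √(0.30 × 0.70 / 40) = 0.072, or about 7 points. This stands. It limits the weight of the point, although the error runs in one direction.

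Two stronger readings are tempting, and the document supports neither.

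- **That the 12-week interval after CR is the main fault and lengthens median PFS by many weeks.** Putting everyone on a 12-week rather than a 4-week schedule, with a true exponential median of 40 weeks, would give Kaplan-Meier medians of 48 and 40. That is late detection on a coarse visit grid: at week 36 the true curve is 0.5^(36/40) = 0.536, still above one half, so the next visit, week 48, becomes the median. It does not measure the censoring rule, and changing the censoring date would not remove it. Nor is it this protocol, where only patients with confirmed CR move to 12 weeks; that is 20 to 40% of patients at the design's CR rates.
- **That the schedule builds in a link between CR and PFS that props up the trial's rationale.** The Discussion links CR to survival, and OS does not depend on examination dates. The article plans no comparison of PFS by CR status.

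**Conclusion.** The point holds as a defect in the stated censoring rule. Taken literally, the rule counts unexamined time as progression-free and biases PFS upward. Under the assumed rates, the excess at 52 weeks is about 0.7 to 1.0 percentage point if examinations are complete. It is about 2 to 5 points if 10 to 30% of patients stop examinations while known alive. The driver is stopped or missed examinations, for which the article gives no rate, rather than the 12-week interval as such. Later detection of progression after CR is a separate limitation.

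PFS is secondary and untested. The primary CR analysis, the 38 patients calculated (40 at most) and the decision rule are unaffected.

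**What to change.** Replace the censoring clause with: PFS is censored at the date of the last evaluable CT or endoscopy showing no progression, or at registration if there is none. The OS rule can stay as it is.

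This is a change of wording that uses data already collected. It adds no visit and leaves the sample size and primary analysis alone. The only cost is that PFS may look slightly shorter. An interval-censored estimate of PFS would address late detection under the 12-week schedule. It is optional, and the point does not depend on it.
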